#### Impact Evaluation Analyses

Based on local data from the participating LHDs, we aim to recruit 400 children across the four LHDs. We will match each case by 20 controls, resulting in a total of 8,000 controls. This will provide 90% power to detect a 20% difference in the number of health service use occasions, including outpatient visits and hospital admissions between intervention and comparison groups. Having 400 cases will also provide the power of 90% to detect a within-group 20% decrease in the number of health service use occasions. This sample size will also allow us to detect a clinically important difference (4.36 points) for child health related quality of life in children post- vs pre-intervention change in the PedsQL4.0 Total Scale Score [9].

We will calculate rate of health service use (e.g. ED, hospital admissions and OP visits) in person-years for the intervention and comparison groups during the baseline (3 years prior to enrolment) and the intervention period (12 months after enrolment), respectively. To assess the effectiveness of this intervention, we will conduct multivariable Poisson (negative binomial if over-dispersion is present) regression analysis with intervention status (intervention versus comparison) as the main independent variable and the rate of health service use (ED, hospital admissions and OP visits, separately and combined) during the intervention period as the outcome variable.

To examine how health service use changes over time between intervention and comparison groups, we will analyse rates of health service use during baseline and intervention periods using mixed effect Poisson regression models, including the interaction term between intervention status and time (after RuralKidsGPS implementation versus before RuralKidsGPS). In all regression analyses, we will control for participant socio-demographics (e.g., age at enrolment, sex, Aboriginal and Torres Strait Islander status, socio-economic status) and clinical factors (e.g., type and severity of health conditions), and baseline rate of health service use. Considering potential clustering effect by site, we will use the generalised estimating equations (GEE) approach in the regression analysis.

Additionally, we will plot monthly rate of health service use for both intervention and comparison groups over baseline and intervention periods. We will undertake an interrupted time series (ITS) analysis to gain a better understanding of how the effect of intervention changes over time (e.g. to identify when the intervention starts to take effect). ITS is one of the most effective quasi-experimental evaluation methods and has been used in many health intervention evaluations [13]. An ITS analysis allows us to control for time-varying confounders such as seasonality and co-occurring competing interventions, thereby addressing important threats to internal validity and causal inference. Figure 4 illustrates using ITS to measure change before and after intervention.

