### Study cohort

The study population includes CYP with medical complexity aged 0 to 18 years, referred for care coordination, who meet the following criteria:

– A diagnosis expected to last at least 12 months– And if ≥ 6months of age, frequent use of health services within the last six-month period, defined as:Two or more ED presentations, ORHospital admission for seven days or more, ORTwo or more outpatient appointments.

A cohort of CYP meeting these criteria and referred for care coordination, their parents and guardians, and clinical and non-clinical staff involved in the planning and/or delivery of the RuralKidsGPS model of care, will all form a part of the study cohort.

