**Figure 3 F3:**
[figure not shown]
Sources of data for linkage.

The comparison group will be identified using the linked administrative health data (ED presentations, hospital admissions, and OP appointments) and frequency matched with 20 children (to each case) by clinical diagnosis, year of birth, sex, local health district who and meet the eligibility criteria for health service use within the past 6 months (outlined in the Study Cohort section above) but who did not access RuralKidsGPS. A population-level evaluation will also be conducted which will include all CYP in the 4 health districts meeting the inclusion criteria.

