Outcome data will capture changes to parent and child reported quality of life assessed using the validated instruments EQ5D5L15 (parent) [8] and Paediatric Quality of Life Inventory (PedsQL4.0), and Child Health Utility 9D (CHU9D) [10] (internal consistency 𝛼 = 0.89 children and 0.92 parent report). These utilities will be included in the estimation of QALYs (quality-adjusted life-years) by calculating the area under the curve, assuming a linear change between the survey dates. QALYs calculated for the year before the intervention starts are based on the health state utility measured at baseline, which was assumed to be stable during the year before.

Cost-effectiveness will be expressed as incremental change in costs (measured by ED presentations, hospital admissions, or OP visits averted), and cost-utility by changes in QALYs gained. Cost-effectiveness will be measured between pre and post implementation of the intervention and calculated according to the formulas below:

\[\begin{array}{l}
Effect\ differences:\ \Delta QALYs = QALY{s_{post\ new\ model\ of\ care}} - QALY{s_{pre\ new\ model\ of\ care}}
\end{array}\]

\[\begin{array}{l}
Cost\ differences:\ \Delta Total\ costs = Total\ cost{s_{postnew\ model\ of\ care}} - Total\ cost{s_{pre\ new\ model\ of\ care}}
\end{array}\]

Imputation methods will be applied to missing values and sensitivity analyses will be conducted for key cost parameters in the data sets to ensure the robustness of the estimates. An additional bootstrap analysis with random 1,000-fold resampling of the original population will be conducted to ensure the validity of confidence intervals.

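### The fixed 3-year baseline cannot exist for children under 3; if their birth stay counts as an admission, within-group admissions and pre/post costs fall with no true effect

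*Protocol article*

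**What the plan says.** - **Eligibility (Study cohort).** Children "aged 0 to 18 years" may enter. The service-use criterion starts only at 6 months ("And if ≥ 6months of age, frequent use of health services within the last six-month period"), so younger infants are admitted without it.
- **Periods (Impact Evaluation Analyses).** Rates per person-year are calculated for both groups over "baseline (3 years prior to enrolment" and "the intervention period (12 months after enrolment), respectively". No rule is given for a child younger than the baseline is long.
- **Use of the baseline (same section).** The 400 cases are said to give 90% power to "detect a within-group 20% decrease in the number of health service use occasions". The baseline rate is a covariate in every regression, and a group-by-time interaction is planned. ED, admissions and outpatient visits are analysed separately and combined.
- **Comparison group (Health Service Use).** Twenty children per case are matched "by clinical diagnosis, year of birth, sex, local health district".
- **Costs (Economic evaluation).** Cost and QALY differences are post minus pre among enrolled children, with no comparison group in the formulas. Average unit costs are applied to each type of activity.

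**The concern.** The eligibility rule and the baseline rule cannot both be met for a child under 3. Using person-years deals with the shorter window. It does not deal with a one-off event at the start of that window. Nearly every child has a birth episode, and it cannot happen again after enrolment. If it is counted, each child under 3 carries one extra baseline admission, and the shorter the window, the more it raises the rate. Children aged 3 or over carry none.

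At stake are the contrasts that compare enrolled children with their own past: the within-group change in admissions and the pre/post costs. Nothing in either removes a fall that was bound to happen, and a reader would take it as a benefit of care coordination.

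**Working it through.** **The stated 90% power.** It can be neither reproduced nor refuted, because no alpha, event rate, over-dispersion or within-child correlation is given. Assume two-sided alpha 0.05, a rate ratio of 0.8 and independent Poisson periods, with SE² = 1/(400·m·T) + 1/(400·0.8·m), where m is the yearly rate and T the baseline length in years. The within-group 90% then needs m of about 1.2 with T = 1. With T = 3, power is 84% at m = 0.7 and 94% at m = 1.0. The point below does not depend on this.

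**One child.** Let λ be a constant true admission rate, with no intervention effect, and a < 3 the age at enrolment. If the birth stay counts as one admission, the expected baseline rate is λ + 1/a and the follow-up rate is λ. The apparent fall is 1 − λ/(λ + 1/a).

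| λ per year | a = 0.25 | a = 0.5 | a = 1 | a = 2 | a = 2.9 |
|---|---|---|---|---|---|
| 1 | 80% | 67% | 50% | 33% | 26% |
| 4 | 50% | 33% | 20% | 11% | 8% |

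**Whole cohort, pooled events over person-years.** Let s be the share under 3 and P the mean baseline person-years per child. The fall is (s/P)/(λ + s/P). Two assumed age mixes, with mean ages 0.5 (under 1) and 2 (1 to 3):

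- Mix A: 5% under 1, 15% aged 1-3. P = 0.05·0.5 + 0.15·2 + 0.80·3 = 2.725; s/P = 0.20/2.725 = 0.073.
- Mix B: 10% under 1, 15% aged 1-3. P = 0.10·0.5 + 0.15·2 + 0.75·3 = 2.600; s/P = 0.25/2.600 = 0.096.

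| Rate per year | Mix A | Mix B |
|---|---|---|
| Admissions, 0.6 | 10.9% | 13.8% |
| Admissions, 1 | 6.8% | 8.8% |
| Admissions, 4 | 1.8% | 2.3% |
| Combined occasions, 4 | 1.8% | 2.3% |
| Combined occasions, 6 | 1.2% | 1.6% |
| Combined occasions, 10 | 0.7% | 1.0% |

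Simulations with between-child variation agree: mean log ratios were −0.07 to −0.10 at 1 admission per year, −0.15 at 0.6 and −0.03 at 4. They were about 0 with the birth stay excluded.

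**Sensitivity to the age mix** (ages uniform within 0-3). With one sixth under 3, as under uniform ages 0-18, the fall in admissions is 10.8%, 5.7%, 2.9% and 1.5% at 0.5, 1, 2 and 4 per year. With 30% under 3 it is 19.0%, 10.5%, 5.6% and 2.9%.

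**False positives within group.** In simulations of 400 children at 1 admission per year, a significant fall (nominal 2.5%) appeared in about 17-18% of trials with one sixth under 3, and in about 48% with 30% under 3.

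**Costs.** With one average unit cost per admission and costs put on a per-year-alive basis over the same window, the admission component falls by the same percentage as the admission rate. No unit costs or length of the cost pre-period are given, so no money figure can be derived.

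**Between groups.** The main model's outcome is use after enrolment, which contains no birth stay. When simulated with case infants always younger than comparison infants born in the same year, the log ratio under no effect was only −0.02 to −0.06, with 6-8% false positives. Entering the baseline rate raw or logged gave nearly equal SDs of the effect (0.077 v 0.075, 0.087 v 0.085, 0.086 v 0.086). In the before/after comparison between groups the artefact cancels at equal ages and rates (ratio of ratios 1.00).

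**The case against.** The article does not say that birth stays are counted. That is an extraction rule which a fuller plan may settle, and the figure of linkage sources is not shown. This stands, and it makes the sizes conditional. The missing age rule is not conditional: the article fixes 3 years and admits newborns.

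The plan also has protection between groups: rates in person-years, matching on year of birth, adjustment for age at enrolment, and both groups shown in the time plots. This also stands, and it limits the point to the contrasts without a comparator.

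Four stronger readings are tempting, and the documents do not support them:

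- A reader might set the 7-14% against the 20% target. That target concerns all service-use occasions, where the artefact is about 1-2%. From 6 months of age, one route to eligibility is two outpatient appointments in six months, equivalent to 4 a year, so very low combined rates are unlikely.
- A reader might infer that the effectiveness estimate is biased towards the intervention. The simulated effect is small even with the age gap always in one direction. Nothing in the matching rule sets a direction, and the reverse gap works against the intervention.
- A reader might object to "QALYs calculated for the year before the intervention starts" for infants not yet born then. Baseline utility applied to one pre year against one post year acts as an annualised reference. Counting only lived time would itself create a QALY gain.
- A reader might call for matching within a month of age, a log-transformed baseline or a main analysis without infants. None is shown to be needed once the birth episode is excluded.

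**Conclusion.** The point holds within limits. A 3-year baseline is impossible for children under 3, and the plan states no alternative. If the birth episode is among the linked admissions, the within-group admission rate falls with no true effect by about 7-14% at 0.6 to 1 admission per year, or about 2-3% at 4 per year, with 20-25% of children under 3. The pre/post comparison then shows a matching spurious saving in admission costs on a per-year basis. These sizes rest on an assumed age mix, assumed constant rates and one counted birth admission per child, none of which the article gives. ED and outpatient rates are untouched, combined use moves by about 1-2%, and the main between-group model is little affected. It is worth correcting because admissions are to be reported separately, the cost formulas have no comparator, and the correction is cheap.

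**What to change.** 1. Define baseline as the shorter of 3 years and time since birth, with actual person-time as the denominator.
2. Exclude the birth episode and contiguous neonatal transfers from baseline counts and costs, in both groups.
3. Annualise pre-period costs over the time the child was alive.
4. Add a sensitivity analysis of within-group admissions and pre/post costs that excludes children under 1 year (or under 3).

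The cost is wording in the analysis plan, one data-extraction rule applied to both groups, and one extra analysis. Recruitment, matching and the main between-group model stay as they are.

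### The before/after interaction model is mixed Poisson with GEE by site; neither gives dependable intervals if a child's own rate of service use changes between periods

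*Protocol article*

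**What the plan says.** All of this is in the protocol article under Impact Evaluation Analyses.

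- **Post-period model.** To assess effectiveness, "we will conduct multivariable Poisson (negative binomial if over-dispersion is present) regression analysis with intervention status" as the main explanatory variable. The outcome is the rate of ED, admission and outpatient use in the 12 months after enrolment.
- **Before/after model.** Change over time between the groups is analysed over the 3-year baseline and the follow-up year, "using mixed effect Poisson regression models, including the interaction term between intervention status and time". The alternative given for the post-period model, "negative binomial if over-dispersion is present", is not repeated. The level and structure of the random effects are not given.
- **Clustering.** After a sentence on adjustment in all regressions: "Considering potential clustering effect by site, we will use the generalised estimating equations (GEE) approach in the regression analysis".
- **Size.** "we aim to recruit 400 children across the four LHDs"; "We will match each case by 20 controls, resulting in a total of 8,000 controls". The Study design section names four local health districts.

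**The concern.** The study is not randomised, so the group-by-time interaction on the primary outcome matters: it is the estimate that removes fixed differences between the groups. The Health Service Use section also makes change in utilisation a stated comparison.

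A child random intercept absorbs differences between children that stay constant over the four years. It does not absorb a child's own rise or fall between periods, and that variation enters the interaction directly.

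The article gives reason to expect such change. Children aged six months or more qualify through heavy use in the preceding six months, and comparison children must meet the same rule, so entry is tied to a recent and possibly temporary state. Ages run from 0 to 18 years, so for some children the baseline covers infancy.

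At stake is an interaction declared significant too often when nothing has changed.

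**Working it through.** **Inputs from the article.** 400 intervention and 8,000 comparison children; 3 years before and 1 year after enrolment; four sites. **Assumed, because the article gives none:** event rate λ per child-year, variance φ of the child-level rate multiplier, correlation r of that multiplier between periods, and a two-sided 5% level.

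**1. The plan's own figure.** The article states: "This will provide 90% power to detect a 20% difference in the number of health service use occasions". This concerns the group comparison, not the interaction, and it can be neither reproduced nor refuted without a rate, a dispersion and a significance level. With negative binomial dispersion k and a rate ratio of 0.8, the variance of the log rate ratio is (1/(0.8λ) + k)/400 + (1/λ + k)/8000. Power of 90% is reached, for example, at λ = 1 with k ≈ 0.57, or λ = 4 with k ≈ 1.5. Rates of 1 and 4 per year are therefore compatible with the stated power and are used below.

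**2. Child-intercept Poisson: reported against true variance of the interaction.**

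- Reported: V_P = 1.05 × [1/(400λ) + 1/(400 × 3λ)], where 1.05 = 1 + 400/8000.
- True, if rates change within child: V_P + 1.05 × 2φ(1 − r)/400.
- False-positive rate: P(|Z| > 1.96/R), with R = √(true/reported).

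Worked case, λ = 4, φ = 1.5, r = 0.5:

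- V_P = 1.05 × (1/1600 + 1/4800) = 0.000875, so SE = 0.030.
- Added term = 1.05 × 1.5/400 = 0.0039375. The total is 0.0048125, so SE = 0.069.
- R = 2.35 and 1.96/2.35 ≈ 0.84, so the false-positive rate is 40%.

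| λ | φ | r | R | By formula | By simulation |
|---|---|---|---|---|---|
| 4 | 1.5 | 1 (constant rates) | 1.00 | 5% | 4–6% |
| 1 | 1.0 | 0.8 | 1.14 | 9% | 9–10% |
| 1 | 1.5 | 0.6 | 1.38 | 16% | 15–18% |
| 4 | 1.0 | 0.7 | 1.67 | 24% | 24–25% |
| 4 | 1.5 | 0.8 | 1.67 | 24% | 24–26% |
| 4 | 1.5 | 0.5 | 2.35 | 40% | 39–43% |

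The simulation column is the range over repeated runs with no true effect. Standard errors clustered on the child gave 4 to 7% throughout.

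**3. A different form of variation.** Here a stable child effect (variance 1) is combined with independent child-by-year variation of variance w. With w = 0, the ratio of model SE to true SD is 0.98 to 1.00 and 95% intervals cover 94.6 to 94.9%. With w = 0.1, the ratio is 0.94 at 1 event/year and 0.75 at 4/year. With w = 0.5, it is 0.71 (coverage 83%) and 0.44 (coverage 61%). The most extreme case tried, 8/year with w = 1, gave 0.25. Child-level robust intervals covered 94 to 96% throughout.

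**4. GEE with site as the cluster.** With four equal sites and no true site effect, the site contributions to the uncorrected sandwich sum to zero. The variance then behaves like 3/4 of an unbiased estimate on 3 degrees of freedom. Rejection at 1.96 has probability P(|t₃| > 1.96 × √0.75 = 1.70) ≈ 19%. Simulation gave 17 to 21% in every setting, including constant rates.

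**The case against.** **The random-effect structure is open.** The article says only that the model is mixed Poisson. A mixed Poisson model is itself a model for over-dispersion, and one with a child time slope or an observation-level effect would fit the wording and be sound. An article may leave such detail to a fuller plan. This stands in part: the plan does not commit to a wrong structure. But a random intercept is the usual reading, and the over-dispersion provision that the article does write down stops short of this model.

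**GEE comes with a robust variance.** A reader might infer that clustering by site leaves a child's repeated counts unprotected. That is not so: children are nested in sites, so a site-clustered sandwich in principle covers any correlation within a child and tolerates a wrong Poisson variance. Its failing is that there are only four clusters. In addition, GEE is a marginal method and does not combine with a mixed model as written.

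**The narrowing is not certain.** A reader might also infer that the intervals will be far too narrow. The documents give no rates, variances or correlations, so they do not support that. With stable child rates the child-intercept model is correct.

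**This is not the named effectiveness analysis.** That is correct. The post-period model is the one tied to effectiveness and carries the negative binomial provision; an interrupted time series analysis is also planned.

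**Conclusion.** The point holds as a conditional one. The over-dispersion provision covers the post-period model only, and the two usual readings of the plan for the interaction are both undependable. A child-intercept Poisson model gives intervals that are too narrow whenever children's own rates change between periods: about 5% false positives with constant rates, 9 to 25% with moderate change and about 40% at the upper end of what was tried. An uncorrected four-site sandwich gives about 17 to 21% whatever the rates do. The first set of figures rests on assumed rates of 1 to 4 events per year, φ of 1.0 to 1.5 and r of 0.5 to 1. The second rests on four sites, no small-sample correction and no true site effect.

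The consequence is confined to the change-over-time estimate. It does not reach the post-period model, and the text gives no ground for saying the main effectiveness test is invalid. It should be corrected before the linked data are analysed, but it is not a fault that by itself undermines the evaluation.

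**What to change.** For the interaction model, state one approach in place of the present combination of mixed Poisson and GEE by site:

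- a marginal Poisson or negative binomial model with a log person-time offset, robust standard errors clustered on the child (or the matched set), and site as fixed effects; or
- a mixed Poisson model with a child random intercept plus a child random time slope or an observation-level effect, and site as fixed effects.

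Either should apply from the outset and not depend on a test for over-dispersion.

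The cost is one sentence in the analysis section and no new data. Intervals will be wider if rates vary within child, and essentially unchanged if they do not.

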### Impact evaluation

#### Health Service Use

A cohort-level evaluation of health utilisation (primary outcome) will be conducted. A cohort of children receiving the RuralKidsGPS will be recruited from the participating LHDs. Routinely collected administrative health data for these children will be requested and linked by an independent group, the NSW Centre for Health Record Linkage (CHeReL) (Figure 3). Using this deidentified linked data, we will compare the change and trend in health utilisation of children (ED presentations, hospital admissions, and outpatient (OP) appointments) who received RuralKidsGPS, to that of a matched comparison group.

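### In the before/after Poisson model, child-level covariates entered as main effects leave the group-by-time term essentially crude, so unmatched factors that affect the change are not controlled

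*Protocol article*

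**What the plan says.** Under Health Service Use, the article sets the comparison in terms of change: "we will compare the change and trend in health utilisation of children" who received the service against that of a matched group. The comparison group is frequency matched, 20 to each case, on clinical diagnosis, year of birth, sex and local health district. It must also meet the recent-use criterion. Severity, Aboriginal and Torres Strait Islander status and socio-economic status are not matching factors.

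Impact Evaluation Analyses describes two regressions. The first, introduced as the assessment of effectiveness, models the intervention-period rate with group as the main variable. The second addresses change over time. It is a mixed effect Poisson model fitted to the rates in both windows, and the effect is read from a product term: "including the interaction term between intervention status and time". No other interaction is named.

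One adjustment statement covers both: "In all regression analyses, we will control for participant socio-demographics (e.g., age at enrolment, sex, Aboriginal and Torres Strait Islander status, socio-economic status". The same sentence goes on to list, as further covariates, "clinical factors (e.g., type and severity of health conditions), and baseline rate of health service use". For clustering by site, "we will use the generalised estimating equations (GEE) approach in the regression analysis". Rates are computed "during the baseline (3 years prior to enrolment) and the intervention period (12 months after enrolment), respectively".

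**The concern.** The study is not randomised. Cases are children referred for care coordination, while comparators are found in administrative records. A difference in severity or social mix within matching strata is plausible, although the document does not show one. For the three unmatched factors, regression adjustment is the stated protection.

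In the before/after model the quantity of interest is a ratio of ratios. Each listed covariate is fixed within a child, so as a main effect it shifts that child's overall level and not the child's change. A factor that is unevenly distributed and goes with a different time course would stay in the group-by-time estimate, which would nonetheless be reported as adjusted for it. If use in more severe children would have risen or fallen anyway, part of that movement would be charged or credited to the service.

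**Working it through.** **Inputs from the article.** 400 cases; 20 comparators each (400 × 20 = 8,000, as stated); 3 years before and 12 months after enrolment; ages from 0 to 18; a design difference of 20%. The article gives no figure for this point, and no event rates or covariate distributions.

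**Step 1: algebra, Poisson model.** For child i in group g (1 = case, 0 = comparator) and window t (0 = before, 1 = after), with exposure E_t common to all children:

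mean = E_t × exp(α + βg + γt + δgt + x_i′b)

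With group, time and their product in the model, maximum likelihood makes the fitted total equal the observed total Y_gt in each of the four cells:

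Y_gt = E_t × exp(α + βg + γt + δgt) × S_g, where S_g = Σ exp(x_i′b) over group g.

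S_g does not depend on t, so

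(Y_11/Y_10) ÷ (Y_01/Y_00) = exp(δ).

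The covariates and exposures cancel, and the estimate is the crude ratio of rate ratios whatever x is.

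**Step 2: random intercept.** Given a child's total count, the after-count is binomial with probability E_1·exp(γ + δg) / [E_0 + E_1·exp(γ + δg)]. This contains neither x nor the child's random effect. The free intercept and group term absorb the rest, so the same result follows.

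**Step 3: check by fitting.** Assumed: 400 v 8,000; true ratio 0.80; severe share 60% v 30%; severity raises the log rate by 0.5 and changes the after/before log rate by −0.3.

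- One data set, equal windows: crude 0.7031 and main effects 0.7031 in a Poisson GLM, a random-intercept Poisson model, GEE by child and GEE by site. Adding baseline rate still gives 0.7031. Covariate-by-time gives 0.774 to 0.779.
- 100 data sets (Poisson GLM), equal windows: crude 0.731, main effects 0.731 (largest log difference 7e-14), covariate-by-time 0.800.
- 100 data sets (Poisson GLM), shorter baseline for children under 3: crude 0.726, main effects 0.726 (largest log difference 0.011), covariate-by-time 0.795.
- One data set with the shorter baselines: adding baseline rate moved the GLM estimate from 0.719 (crude) to 0.748, still short of 0.80.

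**Step 4: size by hand.** The crude bias factor is (after/before in cases) ÷ (after/before in comparators) when the service has no effect. All imbalances below are assumptions. The first three take 8 contacts a year in severe children and 4 in others.

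| Severe, cases v comparators | After/before, severe / other | Cases | Comparators | Bias factor | True 0.80 reads |
|---|---|---|---|---|---|
| 40% v 30% | 1.2 / 0.9 | 6.00/5.60 = 1.071 | 5.40/5.20 = 1.038 | 1.032 | 0.83 |
| 50% v 25% | 1.3 / 0.9 | 7.00/6.00 = 1.167 | 5.30/5.00 = 1.060 | 1.101 | 0.88 |
| 50% v 25% | 0.7 / 1.0 | 4.80/6.00 = 0.800 | 4.40/5.00 = 0.880 | 0.909 | 0.73 |
| 60% v 30% (Step 3) | e^−0.3 = 0.741 / 1.0 | 1.133/1.389 = 0.815 | 1.066/1.195 = 0.893 | 0.913 | 0.73 |

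In the last row the severe relative rate is e^0.5 = 1.649. The before means are 0.6 × 1.649 + 0.4 = 1.389 and 0.3 × 1.649 + 0.7 = 1.195. The after means multiply the severe part by 0.741. The result agrees with the simulated 0.731.

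**Step 5: balanced case.** With severity at 30% in both groups, the simulated values are crude 0.801, main effects 0.801 and covariate-by-time 0.800. There is no bias to remove.

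**The case against.** The strongest reply is that the article says only that it will control for these factors. Main effects only is an inference, the covariate lists are illustrative, and model terms are often left to an analysis plan. That is fair as to wording. But the article names one interaction and states a protection for every regression, and the model as naturally read does not deliver that protection for the change estimate. This goes beyond missing detail.

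Four stronger readings are tempting, and the document does not support them.

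- *That all confounding of the change remains.* Diagnosis, year of birth, sex and district are matched, and comparators must meet the same recent-use criterion. The gap concerns the unmatched factors.
- *That the adjustment fails throughout.* The effectiveness regression on the intervention period is separate, and there the covariates do move the group coefficient (0.798 to 0.836 in the Step 3 scenario with equal windows). Those figures show movement only, not that either value is right.
- *That the term is exactly crude in this study.* Children under 3 cannot have three years of baseline, and shortened follow-up has a similar effect. The term then moves a little, and more if baseline rate is a covariate, but the bias stays.
- *That the bias has a known size or direction.* The imbalances and time courses above are assumed, and they push the estimate both ways.

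The monthly plots and interrupted time series could reveal courses that already differ during baseline. They would not correct the group-by-time estimate, and they would not separate a difference that emerges only after enrolment from an effect of the service.

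**Conclusion.** The point holds for the before/after model and for the three named factors that are not matched on: severity, Aboriginal and Torres Strait Islander status, and socio-economic status. Entered as main effects, they leave the group-by-time ratio at its crude value when before/after exposure ratios are equal. With truncated baselines the ratio moved by only about 0.01 on the log scale. This follows from the model and does not depend on the scenario.

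Whether bias results depends on two things the document does not tell us: whether these factors differ between the matched groups, and whether they alter the change in use. Under the assumed imbalances the bias was about 3% to 10%, against a design difference of 20%; under balance it was nil. The conclusion rests on reading the covariates as main effects, which is the natural reading but is not stated.

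**What to change.** In the before/after model, state that at least severity, Aboriginal and Torres Strait Islander status and socio-economic status enter both as main effects and as interactions with time. Alternatively, weight comparators to the cases' distribution of these factors before fitting. Report the crude ratio of rate ratios beside the adjusted one, so that readers can see what the adjustment does.

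The cost is one line of specification and a few extra parameters. No new data are needed, because these covariates are already promised for every regression. With 8,000 comparators the loss of precision should be small; in check fits the standard error was no wider. The change deals only with measured factors, and unmeasured differences in time course remain a limitation of the design.
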